## 2.2 Study Design

This is a randomized, double-blind (patients and practitioner), placebo-controlled and parallel design trial. The reporting of the trial will adhere to the CONSORT (Schulz, Altman & Moher, 2010) and STRICRTA (MacPherson et. al., 2010) recommendations.

## 2.3 Sampling Frame

The current study focuses on all the states in Malaysia in order to facilitate the patient recruitment process. As such, all diabetes patients in Malaysia will serve as sampling frame and those who fulfill inclusion criteria of the study will be included.

## 2.4 Sample Size

The sample size calculation is based on previous study (Firouzjaei et al. 2016) where the mean differences of HOMA-IR and standard deviation between two groups were 1.23 and 1.25 respectively. For the mean comparison method of two-sample t-test model, a significance level of 5% z_(1-∂/2)_ = 1.96 and a power of 90% z_(1-ß)_ = 1.28 will be utilized to calculate the required sample size.

**2 x (Z_∂_ + Z _ß_)^2^ x** $\boldsymbol{\sigma}$**^2^ (Noordzij et al., 2010)**

n **= -----------------------**

$\boldsymbol{\delta}$ **^2^**

**2 x (1.96 +** 1.**28)^2^ x (1.25)^2^**

**= -------------------------------- = 22**

**(**1.23**)^2^**

For equal allocation of the two groups, the total sample size required when considering a high dropout rate of 35*%* shall be 60 participants, with 30 participants in each group.

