Acupuncture is a technique involving the insertion of fine needles into specific points on the body surface (British Acupuncture Council, 2019). It has been used for more than 2,500 years since its inception in China (VanderPloeg & Yi, 2009). It is an integral part of traditional Chinese medicine (TCM) or traditional medicine (TM). TM has a long history of use in health maintenance and in disease prevention and treatment, particularly for chronic disease (WHO, 2013). According to the theory of TCM, acupuncture can regulate *qi* and *blood* and have a direct impact on bioavailability of substances of the body (Firouzjaei et al., 2016). Acupuncture has become more established in conventional treatment as an alternative or complement medicine (Elisabet, 2008; Takahashi, 2009).

Acupuncture has been shown to be effective in treating diabetes mellitus in clinical randomized controlled trials (RCTs)(Yang and Liu, 2015; Firouzjaei et al., 2016). According to Tjipto, Saputra & Sutrisno (2014), acupuncture as adjunctive therapy on diabetes mellitus showed significant decreased in fasting plasma glucose (FPG)(P<0.01) and oral glucose tolerances test (OGTT)(P<0.001). Similarly, it had been demonstrated that acupuncture combined with metformin was more effective than metformin alone on homeostasis model assessment-insulin resistance (HOMA-IR)(Firouzjaei et al. 2016)(weight mean difference (WMD) -1.34, 95%CI -1.56, -1.12, P<0.001), which acting as an insulin sensitizer improving insulin sensitivity (Liang and Koya, 2010; Lin et al., 2013) and c-peptide levels through effective treatment against metabolic disturbances such as hyperglycemia (Peplow and David, 2012; Tjipto, Saputra & Sutrisno, 2014), inducing weight loss (Cho et al., 2009; Tur et al., 2014; Firouzjaei et al., 2016) owing to its beneficial influence on hormones such as insulin, cholecystokinin, ghrelin and leptin (Zhang, et al. (2018), improving lipid metabolism (Liang and Koya, 2010; Lin et al., 2013; Firouzjaei et al., 2016) while capable of reducing inflammation (Wei et al., 2015). Additionally, acupuncture is able to control co-morbidity conditions such as anxiety (Frisk et al., 2012; David et al., 2013), depression (David et al., 2013), pain (Manyanga et al., 2014; Helianthi et al., 2016), stress (Mishra et al., 2017), sleeping disorder (Cao et al., 2009; Dong et al., 2017) and hence improved quality of life (Frisk, 2012; Vinjamury, 2013; Xiong et al., 2016).

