# 5. Statistical Analysis

Data will be analyzed using SPSS Statistics 26.0 (IBM Corp., New York, USA). Data will be presented as mean ± SD for continuous parameters and percentage for categorical data. Kolmogoro-Smirnov tests for normality will be performed on each parameter before analysis. Comparisons of background and baseline continuous variables between intervention and control group will be examined using independent t-test, while for categorical variables the chi-square test will be used. Intention-to-treat analysis (ITT) will be performed, and all patients enrolled will be included in the analysis, irrespective of compliance. The missing data is imputed using last observation carried forward method. Paired t-test will be carried out in analyzing the statistical significance of mean pre-post change in the parameters. The changes between groups on two time-points (pre-post) will be conducted using analysis of covariance (ANCOVA) if covariates are present. A repeated measure ANCOVA is performed to compare changes between groups at baseline, week 3/4 (6^th^ visit) and week 7 of intervention while controlling for a confounding variable. Mc Nemar’s test is utilized for matched pair’s comparison. However, if data are not normally distributed, non-parametric tests are used. The significant level for all tests is set at p<0.05 (two-tailed).

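### Section 2.4: 30 participants per group do not leave the required 22 after 35% drop-out; 60 in total supports about 27% drop-out, or about 87% power at 35%

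*Protocol*

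**What the plan says.** Protocol section 2.4 takes its planning values from one cited earlier trial, "where the mean differences of HOMA-IR and standard deviation between two groups were 1.23 and 1.25 respectively". It applies the normal-approximation formula for comparing two means ("For the mean comparison method of two-sample t-test model") with z-values of 1.96 and 1.28, that is, two-sided 5% and 90% power. The formula result is given as 22.

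The next sentence moves from 22 to the recruitment target. "For equal allocation of the two groups", and with a drop-out rate of 35% that the protocol itself calls high, the total "shall be 60 participants, with 30 participants in each group". The step from 22 to 30 is not shown.

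Section 5 plans an intention-to-treat analysis of everyone enrolled, with missing values filled by last observation carried forward (LOCF).

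**The concern.** A drop-out allowance has one job: after the assumed losses, the number still needed must remain. The number recruited is therefore the number needed divided by the proportion retained. Multiplying by one plus the drop-out rate always gives too few, and the gap widens as the rate rises; at 35% it is no longer negligible.

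The combination of 90% power and 35% drop-out is the only justification given for recruiting 60. If 60 does not deliver it, the protocol contradicts its own figures. The claim could then pass into the trial report, where a null result would be read as coming from a design with more power than it had.

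**Working it through.** **Inputs.** Difference δ = 1.23, SD σ = 1.25, z-values 1.96 and 1.28, equal allocation, 35% drop-out and 30 per group, all from section 2.4. Two-sided testing at 5% is confirmed in section 5.

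**1. Reproduce the 22.**

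n = 2 × (1.96 + 1.28)² × 1.25² / 1.23² = 2 × 10.4976 × 1.5625 / 1.5129 = 21.68, rounded up to 22 per group. This agrees with the protocol.

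**2. Find the step from 22 to 30.**

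| Rule tried | Per group | Total |
|---|---|---|
| 22 × (1 + 0.35) = 29.7 | 30 | 60 |
| 22 / (1 − 0.35) = 33.85 | 34 | 68 |
| Inflate the total: 44 / 0.65 = 67.7 | 34 | 68 |
| Inflate the unrounded total: 2 × 21.68 / 0.65 = 66.7 | – | 67 |
| One-sided 5%: 18 / 0.65 = 27.7 | 28 | 56 |
| 80% power: 17 / 0.65 = 26.2 | 27 | 54 |

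Of these, only multiplication gives 30 per group. That it was used is an inference, since the protocol prints no formula. The next step does not depend on it.

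**3. What 30 per group leaves.**

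30 × 0.65 = 19.5 completers per group (39 in total), against 22 (44 in total) required.

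**4. Power among completers, each method compared with itself.**

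Normal approximation: power = Φ(δ√(n/2)/σ − 1.96).

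- n = 22: 0.984 × √11 = 3.264; Φ(1.304) = 90.4%.
- n = 19.5: 0.984 × √9.75 = 3.073; Φ(1.113) = 86.7%.

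The exact t-test uses the noncentral t with 2n − 2 degrees of freedom and the same noncentrality.

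| Completers per group | Normal approximation | Exact t-test |
|---|---|---|
| 19 | 85.8% | 83.9% |
| 19.5 | 86.7% | 84.9% |
| 20 | 87.5% | 85.8% |
| 22 | 90.4% | 89.0% |
| 30 (no drop-out) | 96.8% | 96.3% |

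The loss is about 4 points by either method: 90.4 − 86.7 = 3.7 and 89.0 − 84.9 = 4.1.

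**5. Drop-out that 60 can absorb.**

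1 − 22/30 = 26.7%.

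**The case against.** **The loss is small and conditional.** This stands. It is about 4 points, it arises only if the full 35% is lost, and with no loss 30 per group has about 96% power. But 35% is the case the protocol chose to plan for, and for that case its figure is wrong.

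**Drop-out need not mean a lost outcome.** This stands in part. Section 3 counts pregnancy, missed appointments and medication increases as drop-out, and says withdrawn participants are followed to the end of the study. It also counts failure to attend the assessment, so some outcomes will be missing. Section 2.4 treats drop-out as loss when it inflates for it, and the figures above follow that use.

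**LOCF keeps all 60 in the analysis, so nothing is lost.** This does not rescue the figure. Sections 2.10 and 4 schedule HOMA-IR only at baseline and week 7; section 5 mentions a week 3/4 comparison, but neither section lists a HOMA-IR measurement then. Someone lost before week 7 would carry the baseline forward and contribute no change. If 35% of each group do so, the expected difference is 0.65 × 1.23 = 0.80. Power with 30 per group is then roughly 68% to 84%, depending on whether the SD stays at 1.25 or shrinks because of the zero changes, and on the group means assumed. The documents fix none of this, so no single LOCF power can be stated; all of that range is below the completer figures.

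**Stronger readings that a reader might infer.** One is that type II error rises from 10% to 15%. That sets an exact t-test result against a normal-approximation target. Like for like it is 13.3% against 9.6%, or 15.1% against 11.0%.

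Another is that the planning effect itself is misquoted, because section 1.1 reports for the same cited trial a "weight mean difference (WMD) -1.34, 95%CI -1.56, -1.12, P<0.001" whereas section 2.4 uses 1.23. The documents do not show whether these are the same quantity, and 1.23 is the more cautious: 1.34 in the same formula gives 18.3, or 19 per group. Likewise, that the cited comparison was with metformin alone and not with a placebo needle bears on the choice of assumption. It is not an arithmetic error and the documents give no size for it.

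**Conclusion.** The sentence in section 2.4 is wrong as written. The 22 per group is correct, but 60 participants do not preserve it at 35% drop-out. Sixty supports 90% power by the protocol's formula up to about 27% drop-out; at 35%, completer power is about 87% by that formula and about 85% by the exact t-test. These figures rest on the protocol's own difference and SD, equal drop-out in both groups, and analysis of completers only.

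The error is one of statement. It does not show that the trial is badly underpowered or that it must recruit more people, and a reader should not infer either. Even 34 per group, which the correct division gives, leaves about 22 completers and so 89.0% by the exact t-test; the 90% target is met only by the normal approximation that the protocol uses.

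**What to change.** Keep 60 and correct the sentence in section 2.4 in one of two ways:

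- say that 30 per group preserves 22 completers per group, and so 90% power by the stated formula, provided drop-out does not exceed about 27%; or
- keep 35% and say that power is then about 87% by the stated formula (about 85% by exact t-test).

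Print the inflation rule as n/(1 − d), and note that it would give 34 per group (68 in total, 8 more than planned) if 35% drop-out and 90% power were both to be kept.

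Label whichever figure is used as completer-only, and add that the planned intention-to-treat analysis with LOCF would have lower power if participants who drop out carry their baseline value forward.

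The cost is a change of wording and a slightly less favourable stated figure. No additional participants are needed.

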## 2.5 Study Population

Subjects will be recruited through government or private medical centres, community referral and mass media advertising based on criteria below:

Inclusion criteria**:**

1. Malaysian, age between 30 - 69 years old of either gender and with BMI ≤ 40.0 kg/m²
2. T2DM patients with fasting venous plasma glucose FPG ≥ 7.0 mmol/L (126 mg/dL) and glycated hemoglobin (HbA1c) ≥ 6.5% (Clinical Practice Guidelines [CPG], 2015; WHO, 2016; ADA, 2017)
3. Individuals have had T2DM more than one year
4. Diabetes under oral anti-diabetic agents on a stable dose over the previous 3 months and not under insulin therapy

Exclusion criteria**:**

1. Individuals with acute or chronic health problems (eg. chronic kidney disease [stage 4 and 5]/heart/liver failure, cancer, cardiovascular disease, stroke, physical disability, mental illness, nephrotic syndrome, decompensated congestive heart failure and oedema on the abdomen)
2. Needle phobia or allergy to adhesive plaster
3. Planning to move out from Malaysia within 4 months’
4. Being pregnant, planning for pregnancy or lactating women

## 2.7 Interventions

Subjects will receive ten sessions of real or placebo acupuncture treatment using press needle (PYONEX; 0.2 mm x 1.5 mm made by SEIRIN Corporation) over six weeks. Treatments will be administered by 3 qualified TCM practitioners or acupuncturists. They are required to undergo an intensive training to ensure consistency of the administered intervention. A standard operation procedure will be provided during the training such as identification of the acupoint location, compulsory acupoints to be used in each session, technique in performing the study treatment and the time to press needles after insertion of the needles. They will also be briefed about risk management of the trial during the training. To ensure the practitioners are masked to the group allocation, practitioners are requested not to check for the presence of a sharp tip below the plaster during the intervention***.***

Treatments will be performed twice in a week; however, a once-a-week treatment to a three-times-a-week treatment is permitted, but ten treatments must be completed within six weeks. After all the Pyonex press needles are fixed, acupuncture points will be pressed for at least three times (at 0, 15 and 30 minutes) for about 30 seconds, with the degree that can be tolerated by the subject. The follow-up for any adverse event occurs will be 1 week and the total study period will be 7 weeks. For those who are under lifestyle modification or drug treatment during intervention, they are informed to continue with their existing treatment regimens. Any medication and doses received by the participants will be recorded and monitored during the course of the study to ensure the medications are maintained throughout the study. Subjects are also advised to notify the acupuncturist immediately if there are any changes in their current treatments/circumstances such as personal details, medication or get pregnant (for woman) during the study. Safety or adverse event in each session will also be recorded.

### 2.7.1 Treatment group

The treatment group will receive manual active acupuncture treatments. A standardized treatment with 10 needles at 10 acupuncture points on abdomen area such as Zhongwan (Ren-12), Xiawan (Ren-10), Qihai (Ren-6), Guanyuan (Ren-4), Tian Shu (St-25), Daheng (Sp-15), Shangqu, (M-HN), Jinhe (M-HN)/Qixue (Kd-13), Shuidao (St-28) and Liang Men (St-21) are selected based on literature reviews and recommendation by international experts (Yang and Liu, 2015; Kim et al., 2015; Zhong et al., 2016; Firouzjaei et al., 2016). Modification is allowed, particularly less points according to subject’s symptom during treatment. The number and name of acupuncture points used in each session will be documented. The details of acupuncture points are listed in Table 1.

**Table 1:** Abdominal acupuncture points selected in the trial

| No. | Acupoint | Location |
| --- | --- | --- |
| 1 | Zhongwan (Ren-12) | On the anterior midline, 4 cun above the umbilicus |
| 2 | Xiawan (Ren-10) | On the anterior midline, 2 cun above the umbilicus |
| 3 | Qihai (Ren-6) | On the anterior midline, 1.5 cun below the umbilicus |
| 4 | Guanyuan (Ren-4) | On the anterior midline, 3 cun below the umbilicus |
| 5 | Tian Shu (St-25) | 2 cun lateral to the center of the umbilicus |
| 6 | Daheng (SP-15) | 3.5 cun lateral to the center of the umbilicus |
| 7 | Shangqu | 2 cun above the umbilicus (Ren-10/Xiawan), 0.5 cun lateral to the anterior midline |
| 8 | Jinhe (M-HN) or | 1.5 cun below the umbilicus, 0.5 cun lateral to the anterior midline (Ren-6/Qihai) |
|  | Qixue (Kd-13) | 3 cun below the umbilicus, 0.5 cun lateral to the anterior midline (Ren-4/Guanyuan) |
| 9 | Shuidao (St-28) | 3 cun below umbilicus, 2 cun lateral to anterior midline (Ren-4/Guanyuan) |
| 10 | Liang Men (St-21) | 4 cun above the umbilicus, 2 cun lateral (left) to the midline (Ren-12/Zhongwan) |

All subjects are required to take supine position during the treatments. New, disposable, sterilized, stainless-steel press needles will be utilized and inserted according to the acupuncture point selection sequence. The acupuncture points are disinfected with a 70% isopropyl alcohol cotton. In this study, an irradiating needling sensation (*de qi*) does not have to be achieved. “De qi” is a tingling, numbness, and heaviness feelings that occur after an acupuncture needle has been inserted in the body (National Cancer Institute [NCI], 2017). Unnecessary talking in the treatment room is also avoided***.*** During the 45 minutes needle retention period, subject’s abdomen will be covered to prevent exposure. If the subjects are not fit on that day, they will not be given any treatment and will be requested to come on other day. Similarly, if subject reports discomfort or encounter any adverse effect during intervention, acupuncture therapy will be discontinued and the treatment for that particular session will not be included.

### 2.7.2 Control group

The same procedure and acupuncture points are used for the control group. However, subjects are given placebo which is identical to the press needle except the needle element has been removed and replaced with a blunt knob in all aspects are indistinguishable to the press needles (Figure 2; Fleckenstein, Baeumler, Gurschler et al., 2014).

*
[figure not shown]
*

Figure 2: Real pyonex and pyonex placebo

The press needles and placebos are administered (inserted) according to the product directions and following same procedures (Miyazaki et al., 2009)***.*** The validity and credibility of the device had been well demonstrated in other studies (Fleckenstein, Baeumler, Gurschler et al., 2014; Bai et al., 2015; Schroder et al., 2017). To ensure the practitioner is masked to the group allocation, acupuncturist is requested not to check for the presence of a sharp tip below the plaster during the intervention***.*** Figure 3 demonstrated the schematic diagram of study design.

[figure not shown]

**Figure 3:** Schematic diagram of study design

## 2.8 Study Approval

The study is registered with National Medical Research Register (NMRR), Ministry of Health [NMRR-18-2412-43863] and approved by the Ethics Committee for Research Involving Human Participants (JKEUPM) of Universiti Putra Malaysia (JKEUPM-2018-294). Subjects will be informed of the purpose, procedures and safety of the trial and are free to leave without obligation. Subjects in this study are free to make informed choices in taking part. Written informed consent will be obtained from all the subjects’ prior enrollment of the study

## 2.9 Study Procedure

The procedure of this study is shown in Figure 4.

**
[figure not shown]
 Figure 4: Flow chart of study procedure**

Upon obtaining ethical approval for this study, subjects with T2DM are invited to a screening session. A self-developed screening questionnaire will be administered to identify subjects’ eligibility (Appendix A). T2DM will be confirmed with subject’s HbA1c ≥ 6.5% and morning FPG ≥ 7.0 mmol/L (126 mg/dL) (CPG, 2015; WHO, 2016; ADA, 2017) based on subjects’ diabetes book, medications packages, and clinic follows up cards. Those fulfill all inclusion criteria and granting written informed consent will be recruited (Appendix B). Subjects who are taking part in this study will not have to pay for participating. Similarly, no payment will be provided for their participation in this trial.

## 2.10 Measurements

Measurements are performed at baseline and week 7 of the study. A case record form (CRF) will be developed to ascertain socio-demographics, clinical characteristics, physical examinations and HRQoL information of the participants (Appendix C).

### 2.10.1 Socio-demographics and clinical characteristics

Information such as age, gender, ethnicity, marital status, educational level, personal monthly income, duration of diabetes mellitus, and family history of diabetes mellitus will be self-reported from subjects.

### 2.10.2 Body weight and height

Subjects will be measured for weight in kilogram to the nearest 0.1 kilogram, using a digital scale TANITA model HD-382 weighing machine in a standing position. After each measurement, the weighing machine will be reset to zero. The respondent will be requested to stand on the middle of the weighing machine, with the head looking straight forward, arms by the side with minimal clothed and without shoes.

Height will be measured using SECA body meter model 206 in a standing position without shoes while shoulders are in a normal state using a body meter attached to a rigid wall. The accuracy of this device is 0.05 centimeter. Two measurements will be used for both weight and height and the average of the two values will be used in the analysis. Body mass index (BMI) is calculated as weight in kilogram divided by height in meters squared (BMI=Weight(kg)/Height^2^(m²).

### 2.10.3 Waist Circumference

###

Waist circumference (WC) will be measured using SECA measuring tape to the nearest 0.05 centimeter. Respondent will be requested to stand erect and has relaxed the abdominal muscles. Locate the top of the hip bone (iliac crest) and measure at a level just above the iliac crest, and positioning the tape horizontally. Measurements are taken at the end of normal expiration. Two measurements will be taken and average of the two values will be used for the analysis. Central obesity for Asian population is defined as having WC ≥ 90cm for men and ≥ 80cm for women based on WHO/IASO/IOTF criteria (WHO, 2000). All the above physical measurements such as height and weight, waist circumference will be carried out by researcher.

### 2.10.4 Biochemical Assessment

Samples of fasting morning blood (fasting at least 10 hours) will be collected from each subject by qualified personnel for measuring Homeostasis model assessment–insulin resistance (HOMA-IR). HOMA is a method used to quantify insulin resistance and ß-cell function from basal (fasting) glucose and insulin or C-peptide concentrations. It has been proved to be a robust clinical and epidemiological tool for the assessment of insulin resistance (Mathews et al., 1985).

A total of 10 ml/L or approximately 2 teaspoons of venous blood from cubital vein will be performed using venipuncture method. The blood samples will be analysis at pathology laboratory centre for fasting insulin levels, fasting glucose using heparin tubes and sodium fluoride tubes respectively. In this study, fasting insulin and glucose concentrations will be used to derive the HOMA-IR [fasting serum insulin (μU/ml)×fasting plasma glucose (mmol l-1)/22.5] (Mathews et al., 1985) and blood samples will be disposed in four weeks’.

